## Abstract

**Background:**

Although several guidelines for cardiovascular disease (CVD) management have highlighted the significance of primary prevention, the execution and adherence to lifestyle modifications and preventive medication interventions are insufficient in everyday clinical practice. The utilization of effective risk communication can assist individuals in shaping their perception of CVD risk, motivating them to make lifestyle changes, and increasing their willingness to engage with preventive medication, ultimately reducing their CVD risks and potential future events. However, there is limited evidence available regarding the optimal format and content of CVD risk communication.

**Objective:**

The pilot study aims to elucidate the most effective risk communication strategy, utilizing message framing (gain-framed, loss-framed, or no-framed), for distinct subgroups of risk perception (under-perceived, over-perceived, and correctly-perceived CVD risk) through a multi-center randomized controlled trial design.

**Methods:**

A multi-center 3 × 3 factorial, observer-blinded experimental design was conducted. The participants will be assigned into three message-framing arms randomly in a 1:1:1 ratio and will receive an 8-week intervention online. Participants are aged 20–80 years old and have a 10-year risk of absolute CVD risk of at least 5% (moderate risk or above). We plan to enroll 240 participants based on the sample calculation. The primary outcome is the CVD prevention behaviors and CVD absolute risk value. Data collection will occur at baseline, post-intervention, and 3-month follow-up.

**Discussion:**

This experimental study will expect to determine the optimal matching strategy between risk perception subgroups and risk information format, and it has the potential to offer health providers in community or clinic settings a dependable and efficient health communication information template for conducting CVD risk management.

**Clinical trial registration**: https://www.chictr.org.cn/bin/project/edit?pid=207811, ChiCTR2300076337.

## Introduction

1

Cardiovascular disease (CVD) is the leading cause of death in China, with two out of every five deaths attributed to CVD (1, 2). Over 95% of all CVD deaths are attributable to IHD, stroke, hypertensive heart disease, cardiomyopathy, rheumatic heart disease, and atrial fibrillation (3). Currently, China faces a dual challenge with an aging population and the persisting prevalence of cardiometabolic risk factors, particularly the rates of hypertension, dyslipidemia, and diabetes have reached alarming levels (4), and the burden of CVD is projected to escalate in the future. Therefore, it is imperative to devise effective and robust strategies to raise awareness, improve treatment, and enhance control rates for these conditions.

Lifestyle management and risk factor control form the fundamental to both primary and secondary CVD prevention, as underscored by all major CVD management guidelines (5, 6). Despite this emphasis, implementation and adherence to lifestyle modifications and preventive medication interventions remain inadequate in daily practice (7). CVD risk, which is the likelihood of experiencing a cardiovascular event over a specific time frame (e.g., 10 years), is calculated by mathematically combining multiple predictors (8). Healthcare providers use this information to guide prevention strategies and interventions aimed at reducing CVD risk, such as lifestyle modifications and medication. However, a large number of individuals with risk factors remain unaware of their CVD risk, its implications, and the rationale for medication and lifestyle modification (9). Additionally, lifestyle modification interventions often neglect the individual’s preferences, perceptions, and characteristics, which could potentially contribute to suboptimal risk factor management.

Risk perception serves as a cognitive process influencing health behavior and has been regarded as a critical element in various socio-cognitive theories of health behavior, including the Health Belief Model (10), Protection Motivation Theory (11), and Risk Perception Attitude Framework (12) (Supplementary Table S1). Notably, risk perception has also been confirmed to be a motivational determinant that plays a key role in participation and adherence in health-promoting behaviors in empirical researches (13–15). More specify, CVD risk perception, the belief that the individual is vulnerable to develop CVD (16), could affect health behavior change and maintenance (17). However, most people hold inaccurate perception toward their risk to develop CVD when compared with the objective calculated CVD risk (18), our previous research founded that only 30.1% participants accurately perceived their CVD risk (19). These perception bias may lead to diminished motivation, thereby hindering the exertion of requisite effort to mitigate their risk (20). To address this issue, an educational program was designed and proven to effectively improve risk perception for community residents (21) or risk populations (22) in several studies. However, a ceiling effect was revealed for smoker and obesity subgroups. These findings revealed that future campaigns should target risk populations that remarkably hold risk misperceptions.

Prospect theory, developed by Daniel Kahneman and Amos Tversky in 1979, is a psychological theory that describes how people make decisions under uncertainty (23). Prospect theory suggests that individuals weigh potential health outcomes differently depending on whether they perceive them as gains or losses which can affect health-related decision-making (24). Risk communication plays a pivotal role in shared decision-making processes, informing individuals about their CVD risk level and options for risk reduction, thus correcting inappropriate risk perception (25). Previous research has shown that both ‘what’ is communicated and “how” it is conveyed significantly influence an individual’s understanding of CVD risk levels, empowerment, and autonomy (26, 27). Effective risk communication can guide individuals in shaping their perceived CVD risk, motivating them toward lifestyle alterations, and enhancing their willingness to engage with preventive medication, thereby decreasing their CVD risks and potential future events (28). Although current published guidelines suggest discussing the individual CVD risk with patients, there is limited guidance on the appropriate format and optimal presentation strategies (29). Communicating risk is challenging, and the quality of consultation depends on the interpretation and discussion between healthcare practitioners and individuals at risk (30). However, interpretation has consistently been insufficient, and the delivery of information has been inconsistent. Both parties struggle to comprehend CVD risk, and some practitioners lack confidence in explaining risk scores, resulting in inadequate recall of individual CVD risk, confusion, and misunderstandings (31). Given the limited duration of practitioner-patient risk communication, it is of academic and practical value to investigate and elucidate the framework and substance of CVD risk communication, aiming to furnish practitioners and their intended risk populations with a standardized template.

Prospect theory also emphasizes that individuals may exhibit risk aversion or risk seeking behavior depending on the framing of health information (32). Message framing is a health communication strategy supported by theoretical foundations aimed at encouraging behavior change by presenting information in either positive or negative terms (33, 34). The manner in which information is framed can influence decision-making outcomes (35). Gain-framed messages focus on the benefits individuals would gain from adopting recommended behaviors, while loss-framed messages emphasize the negative consequences of not engaging in positive behaviors or continuing with negative behaviors.

Previous reviews (36–38) indicated that framed messages have a modest yet reliable impact on altering health behavior. However, conflicting findings have emerged regarding the comparative benefits of positive/gain- versus negative/loss-framed messages (33). For example, loss-framed messages have been confirmed to persuade people to adopt cancer detection behaviors (39) and diabetes self-care (40), while gained-framed messages have received considerable empirical support for physical activity and dental hygiene behaviors (37). In addition, the literature on message framing consistently demonstrated that when a behavior or characteristic of the individual is not taken into account, there is no discernible advantage for gain- or loss-framed messages (41). Scholars have suggested that the potential moderators may affect the advantage in magnitude and orientation (42), such as risk perception (32, 43) or the nature of behavior (44). Consequently, it is imperative to prioritize the clarification of the potential interaction between message framing and risk perception on health behavior. Regrettably, only a limited number of intervention studies have been conducted to investigate the impact of message framing on behaviors related to CVD prevention, especially targeted populations with risk perception subcategorizes.

## Objective

2

This pilot study aims to clarify the optimal risk communication strategy by examining the compatibility between message framing (gain-framed, loss-framed, or no-framed) and risk perception subgroups (under-perceived vs. over-perceived vs. correct-perceived CVD risk), using a multi-center randomized controlled trial design in Zhejiang province, China. The specific objectives are as follows:

To evaluate the effect of message framing on CVD prevention behaviors among individuals with moderate and high CVD risk.To design a series of CVD risk communication messages based on message framing, then to implement the intervention program among individuals with different risk perception subgroups in the communities.To determine the optimal risk communication message for CVD risk populations with risk perception categories to achieve better CVD prevention behavior change, continuum maintenance, and risk reduction.

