### Study design

3.1

A multi-center 3 × 3 randomized factorial, observer-blinded experimental design was conducted to evaluate the effect of gain-, loss-versus no frame message and under-, over- versus correct risk perception. This trial will be implemented on the basis of National Basic Public Health Service Program (45) and Zhejiang Province Basic Public Service standards (2021 edition). Those includes essential health services for all citizens and chronic health management for hypertensions and diabetes, such as having a free physical examination opportunity once a year, and the electronic physical examination recorded in the community health care system, so that general practitioners (GP) could provide continuous health management services. This study was approved by the Human Research Ethics Committee of the second affiliated Hospital of Zhejiang University school of Medicine (No.2023-0877). It was registered and approved by China Clinical Trials Center (ChiCTR2300076337). We followed the SPIRIT guidelines, and all participants will be followed up for 3 months (Figure 1).

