#### Sample size

3.4.2

Previous risk communication intervention studies were utilized to estimate the sample size. In our previous survey (46), we observed a baseline proportion of healthy lifestyle adherence at approximately 30% among participants with familiar sample characteristics. For the intervention groups, we anticipate a relative increase of at least 50% (47), with an expected difference of 25% between the gain- and loss-framed groups (39). This corresponds to an estimated effect size (W) for Chi-square of 0.20 (48), aligning closely with recommendations from prior studies (38). To achieve a power of 80%, an alpha error rate of 0.05, a standard deviation of 5%, and an estimated effect size (W) of 0.20, a total of 198 participants will be required for our primary outcome, which measures a healthier lifestyle encompassing physical activity, diet, and prevention medication at 3 months. These participants will be evenly distributed into three groups: gain-framed, loss-framed, and no-frame message interventions. However, considering the dropout rate of 20%, a sample size of 240 participants will be required.

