#### Data analysis

3.8.1

Descriptive statistical analysis will be conducted for all measurements. The distributions of categorical baseline variables will be compared using χ^2^ test among the three intervention groups. The difference in continuous variables will be analyzed using either one-way analysis of variance (ANOVA) or a non-parametric rank-sum test. The differential changes in the primary (i.e., healthy behaviors) and secondary (i.e., risk perception) outcomes at T1 and T2, relative to T0, across the three groups will be assessed using generalized estimating equations (GEE) models. GEE methods were applied to estimate model parameters using a binomial distribution for the variance function, a logit link function, and accounting for clustering via an assumed exchangeable working correlation structure (65). The outcomes will be used as dependent variables (one for each model) and, as independent variables, the intervention arms (no-framed, gain-framed, loss-framed message), the factors time (T0, T1, T2), the covariates (risk perception categories) and their corresponding interaction term. The other potential confounders (i.e., variables with baseline imbalances, study sites) will be added as independent variables to adjust GEE model. An exchangeable working correlation structure will be assumed in order to assess the association between factors and outcomes. The statistical significance of each parameter in the model will be analyzed using a Wald test. To account for the potential occurrence of type 1 errors, a Bonferroni correction will be implemented for all GEE models, with a *p*-value threshold of less than 0.003 indicating statistically significant differences (66). The final model’s results will be presented as estimated odds ratio (*OR*) and 95% confidence interval (*CI*) for each significant prognostic variable. We will also conduct the sensitivity analysis to assess the non-response mechanism (67) and an attrition analysis (68) to identify the differential dropout rates and dropout by group interaction on sociodemographic and pretest variables that may pose a threat the equity of the findings (69). Subgroup analysis was performed for cases that did not pass the manipulation check. The principle of “intention to treat (ITT)” will be applied in conducting all primary and secondary outcome analyses. Moreover, the patterns of missingness would be recorded across variables and time points to provide insight into non-random missingness. Statistical significance will be determined by results with *p* < 0.05 in two-sided tests. The analysis will be carried out using SPSS software for MAC (version 26.0) and R software (version 4.3.1).

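### Objective 3 promises a best message for each risk perception category, but neither the sample size nor the parameter-by-parameter testing can support that; an inconclusive interaction is the likely result

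*Protocol article*

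**What the plan says.** The protocol article describes "A multi-center 3 × 3 randomized factorial, observer-blinded experimental design". Frame is the randomised factor: participants are "assigned into three message-framing arms randomly in a 1:1:1 ratio". Perception category (under-, over- or correctly perceived risk) is classified from baseline data (section 3.4.4).

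Section 2 (Objective) opens with "This pilot study aims to clarify the optimal risk communication strategy" and lists three objectives. The first is the effect of framing on prevention behaviours. The third is "To determine the optimal risk communication message for CVD risk populations with risk perception categories". The Abstract and the Discussion repeat the aim of matching message to category, and the Discussion plans software built on that match.

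Section 3.4.2 (Sample size) uses one chi-square effect size, W = 0.20, with 80% power and alpha 0.05. It arrives at 198 evaluable participants, or 240 with 20% dropout, and adds: "These participants will be evenly distributed into three groups: gain-framed, loss-framed, and no-frame message interventions". Category does not enter.

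Section 3.8.1 (Data analysis) puts arm, time, category and an interaction term in a logit GEE and states: "The statistical significance of each parameter in the model will be analyzed using a Wald test". It sets a Bonferroni threshold of 0.003 for all GEE models, and later gives p < 0.05 as the general significance level.

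**The concern.** Objective 3 is a question about interaction: does the best frame differ between perception categories? With three frames and three categories that question has (3 − 1) × (3 − 1) = 4 degrees of freedom. The plan's stated method looks at the coefficients one at a time. Each is a single pairwise contrast relative to a reference frame and a reference category, so none of them answers the question as a whole.

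The sample was chosen without regard to this question, and each frame-by-category cell will hold only about 20 people. If the interaction tests are inconclusive, there is pressure to fall back on the best-looking frame in each cell, because the objective asks for a named optimum. The Discussion intends to build a tool on the answer.

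There is a side effect for objective 1. In a model with category interactions, and depending on the coding and the order of interaction, a single arm-by-time coefficient may describe the frame effect in the reference category only.

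**Working it through.** **Inputs.** From section 3.4.2: W = 0.20, alpha 0.05, power 80%, 198 evaluable, 240 enrolled, 20% dropout, 30% baseline adherence, a relative increase of at least 50%, and a 25% gain–loss difference. From section 3.8.1: threshold 0.003. From the Introduction: in the team's earlier study "only 30.1% participants accurately perceived their CVD risk". The split of the remaining 69.9% is not given.

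**1. The plan's own figure.** N = λ / W², where λ is the noncentrality giving 80% power.
- 1 df: 7.849 / 0.04 = 196.2, so 197, or 198 for three equal arms. This reproduces the plan.
- 2 df (three arms, binary outcome): 9.635 / 0.04 = 240.9, so 241.
- 4 df (frame by category): 11.935 / 0.04 = 298.4, so 299. At alpha 0.003 it is 504.

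The 198 therefore matches a 1-df test and does not cover even the overall three-arm comparison.

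**2. Power of a joint interaction test.** Completers: 240 × 0.8 = 192. Assumption: the interaction has W = 0.20, so λ = 192 × 0.04 = 7.68.
- alpha 0.05 (critical value 9.488): power 58.5%.
- alpha 0.003 (critical value 16.014): power 21.9%.

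Concrete patterns at 22 per cell (198 / 9):

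| Pattern | 0.05 | 0.003 |
|---|---|---|
| Gain better by 25 points in one category, loss in another, equal in the third (joint test) | 43% | 12% |
| 25-point effect in one category only (joint test) | 20% | 3% |
| 25-point gain–loss difference inside one category (single comparison) | 38.5% | 9.1% |

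**3. Precision inside one category.** Correct perceivers per arm: 192 × 0.301 / 3 = 19.3. Half-width of the 95% interval for a difference of two proportions, both near 45%: 1.96 × √(2 × 0.45 × 0.55 / 19.3) = 0.31. Other pairs of rates between 30% and 70% give 30 to 32 points.

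**4. False interactions under the stated procedure.** Simulation with no true interaction: one time point, logit cell estimates with a 0.5 correction, four interaction coefficients. The cells were 21 per category and arm, or an assumed 19/32/13.
- At least one coefficient below 0.003: 0.5 to 0.8% of trials.
- At least one below 0.05: about 14%.

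**5. If the best frame were read off the cell rates instead.** The 25% gain–loss difference can be relative (45% × 1.25 = 56%) or absolute (45% + 25 points = 70%). The same true rates apply in every category, so there is no interaction. Share of simulated trials in which the observed winner is not the same in all three categories:

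| True rates, control / second / best | Winner differs |
|---|---|
| 30 / 45 / 56% (relative reading) | about 57% |
| 30 / 45 / 70% (absolute reading) | about 15 to 18% |
| 40 / 40 / 40% (no frame effect) | 89% |

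The ranges cover the equal and the 19/32/13 cell sizes.

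**The case against.** The strongest objection is that the plan already has a strict gate. A reader might infer that the promised match would mostly be chance. The documents do not support that: picking the highest cell rate is not a rule they contain, and under the 0.003 threshold they do contain, a spurious interaction coefficient turns up in under 1% of trials. Step 5 is also sensitive to how the 25% is read, and if 25 points is meant the winners usually agree. This stands.

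A reader might also infer that the overall frame effect would be estimated from only a third of the sample. Section 3.8.1 fixes neither the coding nor the order of the interaction, and does not say that objective 1 will be read from one coefficient. That is a possibility to close off, not an established fault.

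Some will say that a joint test and a decision rule belong in a fuller analysis plan, and that the study is a pilot. The first is fair as regards missing detail. But the article does commit to a method, testing parameter by parameter, and that method does not fit objective 3. The pilot label helps only in part: the objective is to determine an optimum, and the sample size is a formal power calculation, so the text does not treat objective 3 as exploratory.

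Finally, the power figures use a single time point. Repeated measures could change them, and the within-person correlation is not given.

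**Conclusion.** The concern holds in a limited form. Objective 3 is worded more firmly than the design allows. Category and interaction are absent from the sample size, and the stated tests address single coefficients when the question is whether the best frame varies by category.

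Even if the interaction is as large as the plan's own W, a joint test would miss it about 4 times in 10 at 0.05 and nearly 8 times in 10 at 0.003. A contrast within the correct-perceived category would be known only to about ±31 points. The expected failure is an unanswered question. A misleading match becomes a serious risk only if winners are named from point estimates, or, to a lesser degree, if the general 0.05 level is used for single coefficients.

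These figures assume 192 completers, a binary outcome at one time point, and the category share from the earlier study. A more uneven category mix would lower power further.

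**What to change.** Six changes, all to wording:

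1. Estimate the overall frame effect (objective 1) from a model without category interaction, or as an average over categories.
2. Test objective 3 with one joint Wald test of arm by category at 3 months (4 df), and state which of the two significance levels applies to it.
3. Label objective 3 exploratory, in line with the pilot label.
4. Report the frame contrasts within each category with 95% confidence intervals.
5. Name no category-specific optimal message unless the joint test is significant.
6. Reword the objective and the Abstract to match.

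The cost is a more modest claim. Recruitment, data collection and follow-up stay as they are, and no extra participants are needed.

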CVD risk communication was not only risk assessment and risk value disclosure, but also about the risk coping guidance. Previous studies have demonstrated the importance of engaging in a conversation regarding individual CVD risk between patients and healthcare professionals in order to maximize the impact of the risk information provided (74). However, effectively delivering comprehensive and consistent risk communication to a large population at risk of CVD poses a significant challenge for healthcare providers and the healthcare system, particularly in China (75). The scarcity of primary healthcare providers further complicates the task of dedicating sufficient time to conduct detailed and in-depth health communication. Our intervention study has the potential to offer health providers in community or clinic settings with dependable and efficient health communication information for the purpose of carrying out CVD risk management. This intervention study can provide health providers in community or clinic with reliable and effective health communication information to conduct CVD risk management. Based on recent research results, we will further develop CVD risk communication software that intelligently aligns risk perception categories with optimal risk communication information, thereby significantly enhancing CVD primary prevention practice.

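### One optimal frame per perception category is promised, but the frame effect is never compared between behaviours, and differing significance across separate models cannot supply that comparison

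*Protocol article*

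**What the plan says.** The third specific objective (section 2) is "To determine the optimal risk communication message for CVD risk populations with risk perception categories to achieve better CVD prevention behavior change"; the same sentence goes on to maintenance of the change and to risk reduction. The Discussion plans software that "intelligently aligns risk perception categories with optimal risk communication information". In both places the message is chosen by perception category, and behaviour plays no part in the choice.

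The Introduction says that "loss-framed messages have been confirmed to persuade people to adopt cancer detection behaviors (39) and diabetes self-care", whereas "gained-framed messages have received considerable empirical support for physical activity and dental hygiene behaviors". It lists risk perception "or the nature of behavior" as moderators that scholars have suggested may affect the size and direction of a frame's advantage. It then carries one of them forward: "it is imperative to prioritize the clarification of the potential interaction between message framing and risk perception on health behavior".

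Section 3.7.1 measures physical activity, diet and preventive medication separately, gives no rule for combining them, and adds CVD absolute risk as the other primary outcome.

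Section 3.8.1 states: "The outcomes will be used as dependent variables (one for each model"), with arm, time, perception category and their interaction as independent variables. It says that odds ratios with 95% intervals will be presented for the significant variables. It sets p < 0.003 for all GEE models and also states a general two-sided 0.05.

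**The concern.** A single recommended frame per category is a statement across behaviours. It assumes either that the frames rank alike for physical activity, diet and medication, or that some stated trade-off settles a conflict. The plan estimates the frame effect for each behaviour in a separate model and never sets those effects against each other. With odds ratios presented for significant terms, a reader will have little to go on except which behaviours crossed the threshold.

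That pattern is a poor guide in both directions. Behaviours with the same true effect will often differ in significance by chance, and behaviours with opposite true effects may all miss the threshold. Either way, the trial could name one message for a category, or report that behaviours disagree, without evidence for the statement.

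**Working it through.** **The plan's own figure.** With W = 0.20, alpha 0.05 and 80% power, a 1-df chi-square needs N = 7.85/0.20² ≈ 197, which matches the stated 198. Then 198 × 1.2 = 238, close to the stated 240. This sizes an overall frame effect. It does not size a comparison between behaviours or an effect within a perception category.

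**Inputs.** The 240 enrolled, the 20% dropout and the 1:1:1 allocation are from the protocol article: 240 × 0.8/3 = 64 per arm. The 30% baseline and the 50% relative increase (to 45%) are from section 3.4.2. The following are assumptions:
- the same two rates apply to all three behaviours;
- the within-person correlation r between behaviours is 0, or 0.1 to 0.3 where stated;
- the perception categories are equal in size, so 64/3 ≈ 21 per cell;
- the comparison is of simple proportions at one visit.

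**Power for one behaviour.** SE = √[(0.30×0.70 + 0.45×0.55)/64] = 0.0845, and 0.15/0.0845 = 1.774.
- At 0.05: Φ(1.774 − 1.960) = 0.43.
- At 0.003: Φ(1.774 − 2.968) = 0.12.

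**Chance that three behaviours with identical true effects give a mixed verdict.** With independent behaviours this is 1 − p³ − (1−p)³, using p before rounding.
- At 0.05 (p = 0.426): 1 − 0.077 − 0.189 = 0.73. A simulation with latent correlation 0.3 gave 0.65.
- At 0.003 (p = 0.116): 1 − 0.002 − 0.690 = 0.31. In the 69% with no significant behaviour, a literal reading of the reporting rule gives no odds ratio for the frame at all.

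A second set of assumptions (45% against 70% within one category, 22 to 27 per cell, latent correlation 0 to 0.3) gave mixed verdicts in 62–74% of simulated trials at 0.05 and 26–37% at 0.003.

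**What a stacked model could add for whole arms (r = 0.1 to 0.3).** The variance of a common frame effect is multiplied by (1+2r)/3 = 0.40 to 0.53. The 95% half-width falls from 1.96 × 0.0845 = 16.6 points to 10.5–12.1 points. Power for a common 15-point effect is 68–80% at 0.05 and 30–44% at 0.003.

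For a full reversal (45% against 30% on one behaviour, swapped on another), the contrast is 0.30 with SE 0.0845 × √[2(1−r)] = 0.113 to 0.100. Power is 75–85% at 0.05 and 37–51% at 0.003.

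**The same contrast within one perception category.** With 21 per cell, the SE for one behaviour is 0.148, so the SE of the contrast is 0.198 to 0.175. Power for the full reversal is 33–40% at 0.05 and 7–11% at 0.003. At 0.05 the test would therefore miss 60–67% of true reversals.

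**The case against.** **The background does not establish that the frames work in opposite directions here.** This stands. The Introduction says only that moderators may matter. Among the three trial behaviours it gives a direction for physical activity alone; cancer detection and diabetes self-care are not trial outcomes. The Discussion adds that reviews have failed to favour either frame for specific behaviours. A reader might infer that the protocol itself predicts conflicting frames, but the text does not support that. The question is open, which is a reason to estimate the difference.

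**No decision rule by significance is written down.** This also stands. A reader might infer that the best frame will be picked by counting significant outcomes. The text makes that possible, through separate models and odds ratios for significant terms, but does not say it. A full protocol or SAP may define how the choice is made. What this document does fix is a single-message objective alongside one model per outcome.

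**One frame per category fits the intervention.** Each participant receives all the videos in one frame and no arm mixes frames, so the practical question is which package to send. CVD absolute risk is an overall primary outcome, and section 3.4.2 words the outcome as one healthier lifestyle. This has force: the trial could not support a package with a different frame for each behaviour. Yet no composite is defined in the article, and a composite would average opposing effects without revealing them.

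**Separate models are standard and the added test is weak.** Both parts are true. Separate models should stay, and the added contrast cannot act as a gate.

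**Conclusion.** The point holds in a limited form. The protocol promises one optimal frame per perception category and contains no direct comparison of the frame effect between behaviours. Differences in significance cannot stand in for it: under identical true effects, the three verdicts split in about 73% of trials at 0.05 and about 31% at 0.003. These figures rest on 64 per arm, 30% against 45% for every behaviour, and independence. The common baseline is the weakest assumption, because medication is measured by prescription in people screened from hypertension, diabetes and dyslipidaemia records.

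It does not follow that the frames do conflict, nor that a formal frame-by-behaviour test would settle the choice. Within a category such a test is too weak to support a claim of agreement. The change is worth making because it uses data already collected and keeps the conclusion within what the trial can show.

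**What to change.** 1. Keep the separate GEE models.
2. Report the frame effect with its 95% interval for every primary behaviour, overall and by perception category, whether or not it is significant.
3. Add one exploratory stacked binomial-logit GEE for physical activity, diet and medication, clustered on participant, with behaviour-specific intercepts. Report the arm-level frame-by-behaviour contrast and the common frame effect.
4. Do not treat a non-significant contrast as licence to name a single frame, least of all within a perception category.
5. Describe any single frame named for a category as provisional, judged from the per-behaviour intervals together with CVD absolute risk.

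The cost is one more model, fuller tables and a sentence limiting the conclusion; no new data are needed. The drawbacks are limited power, and a common effect that is hard to interpret if baseline rates differ between behaviours.
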